**Figure 1 F1:**
[figure not shown]
Players of the intervention.

After discharge from the ICU, intervention patients receive specific discharge forms from the case manager. All treating physicians (ICU, general wards and rehabilitation clinic) are requested to record sepsis-related clinical and social information about the patients and his or her needs. This supports the GP to manage ambulant treatment and special therapeutic needs of the patient like home care, physiotherapy, specific adjuvants *etcetera.*

Both, patients and GPs are trained in evidence-based diagnostics and therapy of the most prevalent sepsis sequelae. The liaison physician trains the GP face-to-face using audiovisual education material to impart knowledge about etiology, symptoms, diagnostic instruments and therapy options of sepsis sequelae.

Patients in the intervention group are educated as well in a face-to-face situation by the case manager to get better information about:

1. the study course,

2. the monitoring program,

3. origin and therapy of sepsis,

4. possible sepsis sequelae,

5. physical and psychological impacts of intensive therapy and

6. coping strategies and self-efficacy.

Patients and GPs receive a written manual, including both training content and monitoring instruments. Manuals are used to support training sessions. The patient manual is based on the Discern-criteria [34]. Patients are contacted every month during the first six months after discharge from ICU and every three months during months 7 to 12 for the monitoring. This telephone interview includes established short form instruments for the most common sepsis sequelae, differing from outcome instruments (see Additional file 3). Based on the monitoring results, patients are encouraged to work toward target agreements in daily life. Patient compliance is requested and monitored in the course.

The liaison physician provides this information to the GP with the help of a stratification of urgency (traffic light scheme). The GP is contacted immediately by phone if a new clinical condition arises and gets information about diagnostic and therapeutic possibilities, whereas the liaison physician is available for supervision and requests. In addition, the patient is asked to visit his/her GP if health problems occur.

### Control treatment

Patients in the control group are treated as usual by their GPs or ambulant specialists without any additional information or monitoring. There aren’t any outpatient sepsis follow-up clinics in Germany.

Due to the lack of sepsis aftercare guidelines in Germany, there is no treatment standard available. Usual care is assessed in control group patients. Qualitative interviews of GPs and patients provide additional information.

### Data collection

Data are collected from patients in questionnaires by trained study staff, initially face to face, and from T2 onwards, by phone call. In addition, GPs and ICU staff are asked to provide clinical information after patients have given their informed and written consent. Data are documented as written case report forms and stored in a protected cabinet.

### Outcome measures

Measurements take place from 3 months before hospitalization (**T-1**, retrospectively) until 1, 6, 12 and 24 months after discharge from the ICU (**T1-4**).

Primary outcome is the health-related quality of life assessed by the Short Form 36 Health Questionnaire (SF-36), a multidimensional construction of physical, mental, social and behavior-related components of well-being and operational capability, validated also for German primary care [35].

Secondary outcomes focus on the most relevant sepsis sequelae, including the assessment of physical activity, level of pain, and cognitive deficits or neuropathic symptoms by established questionnaires, all of which are patient-reported outcomes.

Furthermore, for GP compliance review, treatment and cost-effectiveness analysis, patient rehospitalizations, medication, care needs, mortality, physical therapy and instrumental diagnostic procedures are documented by the primary care provider. GPs are asked to provide details of their practice characteristics.

For clinical analysis, diagnoses and ICU procedures are extracted from the ICU documentation system.

For detailed variable/outcome parameter descriptions see Table 1 and Additional file 4.

**Table 1 T1:** List of variables/outcome parameters

**Variables**	**Time of measurement**	**Instrument used (number of items)**
Intensive care unit (ICU)		
Documentation		
ICU stay	T_1_	Days
Mechanical ventilation	T_1_	Days
Kidney replacement therapy	T_1_	Days
Diagnoses at ICU discharge	T_1_	ICD-10
Focus of infection	T_1_	schematized (13)
Microbiological analysis	T_1_	pathogen cluster (8)
Use of sedatives, steroids	T_1_	schematized (4)
Patient reported		
Educational status	T_1_	schematized (2)
Socio-economic status	T_-1 to 4_	schematized (8)
Outcome measure (patient ratings)		
Health-related quality of life	T_-1 to 4_	Short Form 36 Health Survey (SF-36) (36) [35]
Depressive symptoms	T_1 to 4_	Major Depression Inventory (MDI) (12) [36]
Post-traumatic symptoms	T_1 to 4_	Post-Traumatic Stress Syndrome 10-Questions Inventory (PTSS-10) (10) [37]
Motoric function	T_2 to 4_	Short Musculoskeletal Function (XSMFA-D) (16) [38]
Impairment of swallowing, hearing, smelling	T-_1 to 4_	4-stepped Likert scale (4)
Chronic pain	T_1 to 4_	Graded Chronic Pain scale (GCPS) (7) [39]
Neuropathic symptoms	T_1 to 4_	Neuropathic Symptom Score (NSS) (6) [40]
Nutritional status	T-_1 to 4_	Malnutrition Universal Screening Tool (MUST) (4) [41]
Cognitive status	T_1 to 4_	Telephone Interview of Cognitive Status (TICS-M) (21) [42,43]
Sleep	T_2 to 4_	Regensburg Insomnia Scale (RIS) (15) [44]
Medication addiction	T_2 to 4_	Short form for medication use (KFM) (12) [45]
Patient assessment of care	T_-1, 2 to 4_	Patient Assessment of Care for Chronic Conditions (PACIC) (20) [46,47]
Compliance/adherence	T_-1,2 to 4_	Modified Morisky questionnaire (4) [48]
Activities of daily life	T_2 to 4_	(Instrumental) Activities of daily life (ADL/IADL) (11)
General practitioner (GP) documentation		
Mortality	T_2 to 4_	
Current diagnoses	T_-1,2 to 4_	ICD-10
GP consultation	T_2 to 4_	Number
Stay in hospital	T_2 to 4_	Days
Inability to work	T_2 to 3_	Days
Medication	T_-1, 2 to 4_	agent, dosage
Stay in rehabilitation clinic	T_1 to 4_	Days
Remedies and therapeutic aids	T_2 to 4_	schematized (1)
Nursing level	T_2 to 4_	schematized (2)
Contacts to specialists, diagnostic procedures	T_1 to 4_	schematized (7)

To gain insight into processes, barriers and mechanisms of the intervention, qualitative interviews with patients and GPs are performed on a subsample. In this context, the roles of patients’ relatives are also to be evaluated.

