## Background

Sepsis is a worldwide major health concern with increasing incidence [1]. About 85,000 patients a year survive severe sepsis or septic shock [2,3] in Germany. Main sepsis sequelae include critical illness polyneuropathy/myopathy, cognitive deficits and chronic pain, all symptoms of neuronal degeneration [4-7]. In addition, post-traumatic stress disorder (PTSD) and depression are prevalent after stress exposure in the intensive care unit (ICU) [8,9].

Thus, the majority of sepsis survivors suffer from a considerable deficit in physical and psycho-social functions [10], showing a reduced health-related quality of life [11-13]. In addition to the individual burden, sepsis causes significant health economic costs, about four to seven billion Euro/year for Germany alone, including indirect costs due to loss-of-work [3].

At least, sepsis sequelae are considered to be generic for symptoms after critical illness in general [13], which is of even more clinical and socioeconomic relevance.

To improve care for long-term conditions, coordination of the fragmented process by structured interventions is effective [14]. The British National Institute for Health and Clinical Excellence’s guideline *Rehabilitation after critical illness* states that *‘*evidence is often missing and only incorporates aftercare for up to three months’ [15]. Based on a current systematic review, few follow-up interventions have been published [16]. Of these, Hacking *et al*. observed functional improvement of amputations associated with sepsis by an intensive rehabilitation program [17]. Jones *et al*. presented an increase of physical function in 126 critical illness patients who were provided a self-help manual for six months [18]. A British pilot study of Jackson *et al*., with 21 critical care patients, showed a non-significant reduction of post-traumatic symptoms using an in-house, multifaceted telemedicine program [19]. In contrast, a home-based rehabilitation program for eight weeks did not lead to better health-related quality of life or to better physical function in Australian critical illness patients [20]. A nurse-based translational pilot program that incorporated case management for patients with chronic critical illness was not effective for clinical or psycho-social outcomes [21,22].

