### Data analysis

Randomization process will be proofed using binary logistic regression. The dependent variable logarithmic odds ratio of patient is in the intervention versus control group. As predictors, we use potential confounders (for example, socio-demographic or clinical variables). Primary outcome will be analyzed based on a two-sided t-test. Secondary endpoints will be analyzed depending on scale level, using descriptive or hypothesis generating test procedures. For evaluation of average treatment effects, we will analyze the outcome variables with a generalized analysis of covariance (g-ANCOVA) and control for potential confounders. Based on these results, we are able to adjust means, which are comparable with outcome means of a perfect randomized and balanced design [49,50].

Furthermore, mortality is taken into account. Using survival analysis models, we are able to examine the relationship between mortality and treatment. In this way, we also try to identify mortality risk factors.

Finally, we plan cost-effectiveness analyses. Therefore, we sum up the costs of micro interventions and compare the averages of treatment and control group using g-ANCOVA (see above).

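### Follow-up stays, specialist contacts, diagnostics and diagnoses come from GP documentation only, and the intervention informs that GP in one arm only, so these outcomes are at risk of differential ascertainment

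*Protocol article*

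**What the plan says.** Under Outcome measures, the protocol article names the GP as the source for follow-up utilization: "patient rehospitalizations, medication, care needs, mortality, physical therapy and instrumental diagnostic procedures are documented by the primary care provider". In Table 1 the block "General practitioner (GP) documentation" holds current diagnoses, hospital days, rehabilitation stays, remedies, nursing level, and specialist contacts with diagnostic procedures. The patient-rating block has no item on stays, specialist contacts or therapies.

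Under Intervention treatment, the GP in the intervention arm is trained face to face by the liaison physician and receives the monitoring results. Further channels are:

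- "The GP is contacted immediately by phone if a new clinical condition arises and gets information about diagnostic and therapeutic possibilities"
- "In addition, the patient is asked to visit his/her GP if health problems occur"
- "All treating physicians (ICU, general wards and rehabilitation clinic) are requested to record sepsis-related clinical and social information"; the article says that this supports the GP.

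Under Control treatment, patients are "treated as usual by their GPs or ambulant specialists without any additional information or monitoring". Study design states that the intervention cannot be blinded and that each GP has one patient, in one arm.

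Under Data analysis, the cost comparison is described thus: "we sum up the costs of micro interventions and compare the averages of treatment and control group using g-ANCOVA".

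**The concern.** Improving what the GP knows is part of the treatment, and what the GP knows is also the measuring instrument for these outcomes. An event outside the practice counts only if the GP learns of it and records it. If the program raises that chance in one arm, equal event rates produce unequal recorded rates.

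Costs are part of the stated aim, and the article's conclusion hopes for a cost-effective addition to aftercare. Over-recording in the intervention arm would make the program look costlier than it is. It could also make better recording look like more diagnosis or treatment of sequelae.

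The planned g-ANCOVA does not repair this. It adjusts for potential confounders, whereas unequal capture arises after randomization, in the outcome itself. The limitations section covers a Hawthorne effect and contamination, but not this route.

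**Working it through.** **Step 1: which outcomes are exposed.** Setting the data source beside the information flow gives:

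| Outcome | Source named in the article | Route from intervention to recording |
|---|---|---|
| Current diagnoses | GP | Direct: the GP is phoned about new conditions |
| Rehabilitation stays | GP | Indirect: discharge forms, more GP contact |
| Hospital days, specialist contacts, diagnostics | GP | Indirect: a better informed GP who may see the patient more often |
| GP consultations, GP prescriptions | GP | Little: these are the GP's own acts |
| SF-36, PACIC, Morisky questionnaire | Patient | None by this route |

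**Step 2: size, as an illustration only.** The documents give neither capture rates nor a rehospitalization risk, so every input here is an assumption except the group size. That size, 86 per arm, is half of the 172 patients planned at T2. The 172 reproduces: for d = 0.5 and two-sided 0.05, the exact t-test has power 0.8999 with 85 per arm and 0.9032 with 86.

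Recorded risk = true risk × capture. With equal true risks, the apparent risk ratio is capture (intervention) ÷ capture (control). Intervention capture is set at 95%, and the true risk runs from 30% to 60% in both arms.

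| Control capture | Apparent risk ratio | Chance of a false significant excess in the intervention arm |
|---|---|---|
| 95% | 0.95/0.95 = 1.00 | 2.5% (nominal) |
| 90% | 0.95/0.90 = 1.06 | 4% to 6% |
| 85% | 0.95/0.85 = 1.12 | 7% to 12% |
| 80% | 0.95/0.80 = 1.19 | 10% to 22% |
| 70% | 0.95/0.70 = 1.36 | 21% to 50% |

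The last column uses the normal approximation for two proportions with 86 per arm: Φ[(difference − 1.96 × pooled SE) ÷ unpooled SE]. Example with true risk 50% and control capture 70%: the recorded risks are 0.475 and 0.350, so the difference is 0.125. The pooled SE is √(2 × 0.4125 × 0.5875/86) = 0.0751 and the unpooled SE is √((0.475 × 0.525 + 0.350 × 0.650)/86) = 0.0745. The result is Φ(−0.30) = 0.38.

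**Step 3: masking of a true benefit.** Apparent ratio = true ratio × capture ratio. A true ratio of 0.80 appears as 0.80 × 0.95/0.85 = 0.89 at 85% control capture, and as 0.80 × 0.95/0.75 = 1.01 at 75%.

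**Step 4: costs.** The capture ratio must not be applied to total cost. GP visits and prescriptions should be recorded about equally in both arms. With equal true use, and the program's own costs set aside, the ratio of recorded total costs is a weighted average of 1 and the capture ratio. The capture ratio is therefore an upper bound: 1.12 for 95% against 85%.

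**The case against.** The strongest reply is that no difference in capture is shown.

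- The monitoring calls use symptom instruments. Nothing says that they report admissions, specialist visits or therapies to the GP.
- The Background describes primary care as the setting where all health services are coordinated, which speaks against poor capture in usual care. The sentence "coordination of the fragmented process by structured interventions is effective" is a general remark on long-term conditions and does not say that information fails to reach the GP.
- Data collection states the request for GP information without any difference between arms. Mentioning specialists for control patients does not separate the arms either, since intervention patients may see them too.
- Extra consultations, diagnostics or therapy prompted by the program are real use and real cost, not better recording.
- Additional file 4, with the detailed outcome descriptions, is not shown, and it may name a second source.

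All of this stands as a limit on the point. A reader might infer that the cost, rehospitalization and process-of-care comparisons are biased, or that those aims cannot be answered. The documents do not support that. The size of any difference is unknown, equal capture gives no bias in the ratio, and PACIC and the Morisky questionnaire are patient-rated.

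The reply does not remove the risk. The text and Table 1 name no source for these items other than the GP, that GP is unblinded, and extra information reaches the GP in one arm only.

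**Conclusion.** The GP-documented diagnoses, stays, specialist contacts and diagnostics, and the cost components built on them, are at risk of differential ascertainment. The link is most direct for current diagnoses and indirect for the rest. The likely direction is more events and costs recorded in the intervention arm, so a saving could be understated. The size cannot be derived from the article: under the assumed captures, the apparent risk ratio with no true effect runs from 1.00 to 1.36. The conclusion rests on the article and Table 1 naming the GP as the only source. The SF-36 primary outcome, PACIC, the Morisky questionnaire, GP consultations and GP prescriptions are not materially affected. This is worth correcting because the remedy is cheap, but it does not threaten the primary analysis.

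**What to change.** 1. In the existing T2 to T4 telephone interviews, ask both arms the same short list: hospital stays, rehabilitation stays, specialist contacts and therapies since the last assessment.
2. Treat the answers as a parallel source. Keep GP documentation, including for patients who die or drop out. The article assumes 30% mortality and 40% drop-out, and such patients cannot give a later report.
3. Compare GP-documented and patient-reported counts by arm.
4. Repeat the rehospitalization and cost comparisons with the patient-reported or combined source as a sensitivity analysis. If agreement between the sources differs by arm, limit the cost conclusion accordingly.

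A reader might infer that patient report should replace the GP record. That goes too far: cognitive deficits are expected in this population, and intervention patients are trained and monitored, so recall error may not be the same in both arms. The cost is slightly longer calls, one added comparison and a sensitivity analysis.

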### Data analysis

Randomization process will be proofed using binary logistic regression. The dependent variable logarithmic odds ratio of patient is in the intervention versus control group. As predictors, we use potential confounders (for example, socio-demographic or clinical variables). Primary outcome will be analyzed based on a two-sided t-test. Secondary endpoints will be analyzed depending on scale level, using descriptive or hypothesis generating test procedures. For evaluation of average treatment effects, we will analyze the outcome variables with a generalized analysis of covariance (g-ANCOVA) and control for potential confounders. Based on these results, we are able to adjust means, which are comparable with outcome means of a perfect randomized and balanced design [49,50].

Furthermore, mortality is taken into account. Using survival analysis models, we are able to examine the relationship between mortality and treatment. In this way, we also try to identify mortality risk factors.

Finally, we plan cost-effectiveness analyses. Therefore, we sum up the costs of micro interventions and compare the averages of treatment and control group using g-ANCOVA (see above).

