### Scientific hypothesis

After six months, the intervention group will show an improved primary outcome (SF-36) compared to patients with usual care in the control group.

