### Sample size

A wide range of effect sizes is found in comparable studies. Jackson *et al*. [19] reported that for executive functioning ability a Cohen’s d =1.1 Elliott *et al*. [20] reported that for the SF-36 physical and mental summary scores, Cohen’s d = 0.14/0.13, respectively. For our study, we assume a medium Cohen’s d = 0.5 for our primary outcome, which is between these ‘extreme values’.

With a statistical power of 90% and a significance level of 0.05, we need n = 172 patients at T2 for two-sided tests. Assuming a 40% drop-out rate [24] and 30% mortality [25], 290 patients are needed at T1.

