### Data collection

Patients will be recruited from 20 ICUs in nine study centers across Germany (see Additional file 1). Eligible survivors of severe sepsis or septic shock are screened on a daily basis by ICU consultants and reported to the study team. Within one month after discharge from ICU, patients are contacted by a study physician and asked to participate in the study. For eligibility, a cognition test is performed [26]. All patients are informed about the study course.

Within one month after discharge from ICU, the first data set (T1) is collected by the study nurse, including clinical and socio-demographic characteristics. At the same time, the liaison physician contacts the responsible general practitioner (GP) by telephone to ask for study participation.

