### Randomization

Given the GP’s written consent, patients are randomized in the intervention versus control group with n = 145 patients per group. Randomization sequence is computer-generated and provided in a sealed opaque envelope.

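### The primary SF-36 comparison at six months is an unadjusted t-test although SF-36 is collected at T1; adjusting for T1 is a free gain in precision

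*Protocol article*

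**What the plan says.** **Primary test.** Data analysis: "Primary outcome will be analyzed based on a two-sided t-test". No covariate is attached to it. Scientific hypothesis sets the time point: "After six months, the intervention group will show an improved primary outcome (SF-36) compared to patients with usual care in the control group".

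**Sample size.** The Sample size section assumes "d = 0.5 for our primary outcome", with 90% power and a two-sided 0.05 level, and arrives at 172 patients at T2.

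**Baseline measurement.** In Table 1 (Outcome measures) the row for "Short Form 36 Health Survey (SF-36) (36) [35" runs from T-1, which is retrospective, through T1 to T4. The first Data collection section says "Within one month after discharge from ICU, the first data set (T1) is collected by the study nurse" and places the call to the GP at the same time. The Randomization section continues: "Given the GP’s written consent, patients are randomized in the intervention versus control group with n = 145 patients per group". As described, T1 comes before allocation.

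**Adjusted analysis.** Data analysis also states "we will analyze the outcome variables with a generalized analysis of covariance (g-ANCOVA) and control for potential confounders". Baseline SF-36 is not mentioned there, and this model is not called the primary analysis.

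**The concern.** The primary outcome is measured with the same instrument before allocation and again at six months, but the test that carries the conclusion uses only a two-group comparison. Two things are given up.

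- **Precision.** The part of the variance at T2 that T1 predicts stays in the error term, so the confidence interval is wider than the collected data require.
- **Protection against an observed imbalance.** If one arm starts with better SF-36 scores by chance, part of that difference carries through to T2 and is read as treatment effect or hides it. This is conditional bias: it averages to zero over repeated randomizations but is present in the one trial that is run.

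**Working it through.** **Inputs from the protocol article.** d = 0.5, power 90%, two-sided 0.05 and 172 at T2 (Sample size); equal allocation (Randomization), hence 86 per arm.

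**Assumption.** r, the correlation between T1 and T2 SF-36, is not given in the article. The range 0.2 to 0.7 is used.

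**1. Reproduce the plan's figure.** For an unadjusted two-sample t-test, the noncentrality is d × √(n/2) with n per arm and 2n − 2 degrees of freedom. With n = 86: 0.5 × √43 = 3.28, 170 degrees of freedom, power 90.3%. With n = 85 the power is 89.99%, just short of 90%. So 86 per arm, or 172 in total, is exactly the requirement for the unadjusted test.

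**2. Power with adjustment for T1.** ANCOVA multiplies the residual variance by 1 − r². The effective effect size is 0.5/√(1 − r²), with N − 3 = 169 degrees of freedom. For r = 0.5: 0.5/√0.75 = 0.577, noncentrality 0.577 × √43 = 3.79, power 96.4%.

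| r (assumed) | 1 − r² | CI width relative to t-test | Power at 172 | N for 90% power |
|---|---|---|---|---|
| none (t-test) | 1.00 | 1.00 | 90.3% | 172 |
| 0.2 | 0.96 | 0.98 | 91.4% | 164 |
| 0.3 | 0.91 | 0.95 | 92.8% | 156 |
| 0.4 | 0.84 | 0.92 | 94.5% | 144 |
| 0.5 | 0.75 | 0.87 | 96.4% | 130 |
| 0.6 | 0.64 | 0.80 | 98.3% | 110 |
| 0.7 | 0.51 | 0.71 | 99.5% | 88 |

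The CI width is √(1 − r²). The last column is the smallest even N that reaches 90% with the noncentral t.

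**3. Chance imbalance at T1.** In SD units the T1 difference between arms has standard error √(2/86) = 0.152. Then 0.2/0.152 = 1.31, and the two-sided normal probability of a larger difference is about 19%.

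**4. What such an imbalance does.** An imbalance of 0.2 SD shifts the t-test estimate by r × 0.2:

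- r = 0.3: 0.06 SD, or 12% of the assumed effect of 0.5
- r = 0.5: 0.10 SD, or 20%
- r = 0.7: 0.14 SD, or 28%

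**5. If the t-test were on change from T1.** The article does not say whether the t-test takes the T2 score or the change; the T2 score is the natural reading. For change, the variance factor is 2(1 − r): 1.4 at r = 0.3, 1.0 at r = 0.5 and 0.6 at r = 0.7. The ANCOVA factors are 0.91, 0.75 and 0.51. ANCOVA is more precise under either reading.

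**The case against.** The strongest reply is that nothing here is wrong. In a 1:1 randomized trial the t-test keeps its type I error and, leaving attrition aside, is unbiased over repeated randomizations. Its standard error already allows for chance imbalance, and the sample size was computed for the same test. The article also plans a g-ANCOVA that aims at means free of imbalance. And the gain is unknown: T1 is taken face to face within a month of ICU discharge and T2 by telephone at six months, so the correlation could be low. At r = 0.2 the power gain is about one percentage point.

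Most of this stands, and it limits the point to efficiency and conditional bias. It does not remove it. The g-ANCOVA is not the primary test and does not name baseline SF-36, and even a small gain costs no patients.

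Stronger readings that the article does not support:

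- **That the t-test is invalid or 172 is wrong.** The figure reproduces exactly, and test and sample size agree.
- **That adjustment would make up for most of the power lost to attrition.** A reader might treat the 40% drop-out and 30% mortality as separate losses: 290 × 0.6 × 0.7 = 122 evaluable, with t-test power 78.2%. The article does not state 122; it plans 172 at T2. Even at 122, ANCOVA reaches 81.9% at r = 0.3, which is 3.7 of the 12.1 points lost. It recovers more than half only from r of about 0.4 (84.8%, or 6.6 of 12.1).
- **That adjustment deals with drop-out in general.** It reduces bias only where loss depends on T1 SF-36, and it does nothing for deaths, where no T2 score exists.
- **That the unlisted confounders, or having two analyses, are a defect.** A covariate list is commonly left to the full protocol or SAP, and the article ties the t-test explicitly to the primary outcome.

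**Conclusion.** The point holds as a free improvement, not as a correction of an error. The primary analysis leaves unused a pre-randomization measurement of its own outcome.

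The benefit ranges from slight to large depending on a correlation that the article does not report, so no single figure should be quoted without its assumed r. The protection against a T1 imbalance likewise grows with r, from 12% of the assumed effect at r = 0.3 to 28% at r = 0.7 for a 0.2 SD difference.

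The conclusion rests on two readings. The first is that T1 SF-36 is obtained before allocation: the sequence in the Data collection and Randomization sections implies this, though no sentence says so outright. The second is that the t-test compares T2 scores; the recommendation does not change if it compares change scores.

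**What to change.** State in the Data analysis section, or in the SAP before unblinded data are examined:

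- **Primary:** ANCOVA of the T2 SF-36 score on arm, with the T1 value of the same score as the pre-specified covariate, two-sided 0.05.
- **Sensitivity:** the unadjusted t-test.
- **Supportive:** the g-ANCOVA with further covariates.

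Study center may be added but is optional, because the article describes no stratification by center. It would also help to confirm in one sentence that T1 SF-36 is completed before allocation.

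The sample size need not change; any gain in precision can be kept as a margin. The change needs no extra patients, visits or data.

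Drop-out unrelated to T1 SF-36, and deaths before T2, are not solved by this and need their own handling.

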**Methods/Design:**

In a two-armed randomized multicenter interventional study, patients after sepsis (n = 290) will be assessed at 6, 12 and 24 months. Patients are eligible if severe sepsis or septic shock (ICD-10), at least two criteria of systemic inflammatory response syndrome (SIRS), at least one organ dysfunction and sufficient cognitive capacity are present. The intervention comprises 1) discharge management, 2) training of general practitioners and patients in evidence-based care for sepsis sequelae and 3) telephone monitoring of patients. At six months, we expect an improved primary outcome (health-related quality of life/SF-36) and improved secondary outcomes such as costs, mortality, clinical-, psycho-social- and process-of-care measures in the intervention group compared to the control group.

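### The six-month SF-36 t-test can only compare patients alive and reached, although the plan expects the intervention to change mortality and handles deaths in a separate model

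*Protocol article*

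**What the plan says.** The Scientific hypothesis section sets the endpoint and time: "After six months, the intervention group will show an improved primary outcome (SF-36) compared to patients with usual care in the control group". The Data analysis section names the test: "Primary outcome will be analyzed based on a two-sided t-test". The Sample size section counts the patients for that test at T2, the six-month visit: "With a statistical power of 90% and a significance level of 0.05, we need n = 172 patients at T2 for two-sided tests". It then allows for losses: "Assuming a 40% drop-out rate [24] and 30% mortality [25], 290 patients are needed at T1".

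From T2 onwards patient questionnaires are completed by telephone (second Data collection section), and SF-36 is listed as a patient rating in Table 1. A patient who has died or is not reached therefore has no T2 value.

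Deaths come up in the Data analysis section: "Furthermore, mortality is taken into account. Using survival analysis models, we are able to examine the relationship between mortality and treatment". That section also plans a g-ANCOVA of the outcome variables with control for potential confounders. Neither item says how a death enters the SF-36 comparison. The abstract expects "improved secondary outcomes such as costs, mortality, clinical-, psycho-social- and process-of-care measures in the intervention group", so mortality is among the outcomes that the intervention is expected to improve. The Description of risks section puts six-month mortality above 30%.

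**The concern.** Being alive at six months is decided after randomization, and the plan expects treatment to influence it. If the intervention keeps some frailer patients alive, they enter the intervention mean and pull it down. If mortality moved the other way, the arm with more deaths would look better on SF-36, because its frailest patients would be absent. A separate survival model shows the difference in mortality but leaves the SF-36 comparison as it was. The two results could point in opposite directions, and the article does not say how they would be read together.

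Loss among living patients could also differ by arm. The trial is unblinded, intervention patients are telephoned monthly in the first six months, and controls are not monitored. Rules for missing values in living patients are commonly left to an analysis plan, so it is the treatment of death that carries this point.

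**Working it through.** **Inputs from the protocol article.** Sample size section: "we assume a medium Cohen’s d = 0.5 for our primary outcome"; power 90%, two-sided 0.05, 172 at T2; 40% drop-out, 30% mortality, 290 at T1. Randomization section: "patients are randomized in the intervention versus control group with n = 145 patients per group".

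**Step 1: reproduce 172.** The normal approximation gives 2 × (1.96 + 1.2816)² / 0.5² = 84.1, so 85 per arm. The exact calculation with the noncentral t distribution gives 85.03, so 86 per arm and 172 in total, with power 90.3%. The figure reproduces.

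**Step 2: which loss gives 290.**
- 40% in total: 172 / 0.60 = 286.7, so 287, close to 290.
- 30% only: 172 / 0.70 = 245.7, so 246.
- 40% and 30% multiplied: 172 / (0.60 × 0.70) = 409.5, so 410.
- 40% and 30% added: 172 / 0.30 = 573.3, so 574.

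Only a single 40% loss fits, so it must already contain the deaths.

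**Step 3: who is in the t-test.** 290 × 0.60 = 174, and the stated requirement is 172 (172 / 290 = 59%). If 30% die within the 40% total, that is 87 deaths and 116 − 87 = 29 living patients without a value, or 29 / 203 = 14.3% of survivors.

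**Step 4: bias from unequal mortality (assumed values).** Let m_c and m_i be control and intervention mortality. Assume that the intervention saves some patients and costs no lives, that it has no effect on SF-36 in patients who would survive in either arm, and that saved patients score g SD below the other survivors. Saved patients make up (m_c − m_i) / (1 − m_i) of intervention survivors, so

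shift = −(m_c − m_i) / (1 − m_i) × g.

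- 30% versus 20%: 0.10 / 0.80 = 0.125. With g = 0.5 the shift is −0.06 SD; with g = 1 it is −0.13 SD. That is one eighth to one quarter of d = 0.5.
- Arms reversed: the same size with the sign changed, in favour of the arm with more deaths.
- Equal mortality: zero.

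**Step 5: a second model.** Suppose a normally distributed latent health score, correlated ρ with SF-36, decides who dies. With z_m the normal quantile of mortality m, the survivor mean is ρ × φ(z_m) / (1 − m). With control mortality 30%, ρ from 0.3 to 0.7 and no true SF-36 effect, the shift in SD of control survivors is:
- intervention mortality 25%: −0.02 to −0.06
- intervention mortality 20%: −0.05 to −0.12
- intervention mortality 15%: −0.07 to −0.18
- intervention mortality 30%: zero

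**Step 6: effect on power.** With 86 per arm, power is 90% at d = 0.50, 84% at 0.45, 74% at 0.40 and 63% at 0.35. A shift of 0.06 to 0.13 would take a true 0.50 to between 0.44 and 0.37, inside that range.

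**The case against.** The article does not define an analysis set, forbid imputation or call for complete cases. A reader might infer that living drop-outs are simply deleted. The text does not say so, and a condensed article may leave such rules to the full protocol or analysis plan. This stands, and the point does not depend on it: telephone collection and sizing on patients present at T2 fix that the stated test has no value for a death.

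A reader might also infer that the 30% and 40% accumulate, leaving about 122 (290 × 0.42) or 87 (290 × 0.30) patients. The plan's own arithmetic rules both out. The starting point of the 30% mortality is not given either, and patients enter after ICU discharge, so deaths after randomization may be fewer.

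Loss alone does not undo randomization; loss related to both arm and outcome does. The expected mortality benefit is one item in the abstract's list of secondary outcomes, and no size is given. The g-ANCOVA can reduce arm differences as far as measured covariates explain them. Excess deaths would not be hidden, since mortality is documented from T2 and related to treatment. In the direction that the plan expects, the bias works against the intervention. All of this is fair and limits the size of the problem. It leaves open what the primary SF-36 contrast means when survival differs by arm: neither the g-ANCOVA as described nor the survival model settles that.

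**Conclusion.** The point holds as a possible modest bias. The primary comparison is conditional on survival, which the plan expects treatment to change, and the named test neither says so nor allows for it. Under the assumed 30% versus 20% mortality and a gap of 0.5 to 1 SD, the bias is about 0.06 to 0.13 SD in either direction. A separate frailty model gives 0.05 to 0.12 SD for the same contrast. Both are zero with equal mortality. The mortality contrast, the gap and the correlation are assumptions; the documents supply none of them.

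The stronger conclusion, that the primary comparison is invalid or has lost the protection of randomization, is not supported. It would need a mortality difference and a frailty gap that the documents do not establish. The sample size of 172 is also not in question here. The change is worth making because it is cheap, but the trial does not stand or fall on it.

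**What to change.** 1. State that the primary SF-36 contrast is in patients alive at six months.
2. Replace the unadjusted t-test by an analysis adjusted for T1 SF-36: either ANCOVA with multiple imputation for living patients without a T2 value, or a mixed model over the visits. With a mixed model, say that its estimates are not interpreted beyond death.
3. Add one pre-specified supportive analysis of all randomized patients with known six-month status, with deaths ranked below every survivor and compared by a Wilcoxon rank test. Living patients without a T2 value would enter with imputed values.
4. Report that analysis and the mortality comparison beside the primary result.

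The data are already planned: Table 1 lists SF-36 from T-1 to T4 and GP-documented mortality from T2 to T4. The cost is some analysis wording and programming. Adjustment for T1 SF-36 removes survivor selection only as far as T1 explains it, which is why the supportive analysis is needed. The ranked analysis mixes survival with quality of life and has lower power when mortality is equal, so it should stay supportive and not replace the primary analysis.
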